## Abstract

**Background:**

Smoking remains a leading health risk factor among Europeans. Tobacco, together with other factors, will lead to an expansive epidemic of chronic diseases, including COPD, among the working population in Russia. The general aim of the RESearch on the PrEvalence and the diagnosis of COPD and its Tobacco-related etiology (RESPECT) study is to gain a better understanding of the prevalence, pathogenesis and symptoms of COPD.

**Methods/Design:**

The RESPECT study is a prospective, population-based cohort study of subjects aged 35–70 years in two north-west regions of the Russian Federation (Saint Petersburg and Arkhangelsk). The study includes three components: a cross-sectional study (prevalence), a case-control study and a cohort study (diagnostic). An investigator who interviewed the patient completed three questionnaires. Spirometry, including a reversibility test, was offered to all participants. Individuals displaying forced expiratory volume in 1 s (FEV_1_)/forced vital capacity (FVC) < 0.7 and/or FEV_1_/FVC < the lower limit of normal before and/or after bronchodilation were included in a follow-up study and were examined by a pulmonologist using a standardized comprehensive examination protocol. A future case-control study of two matched groups of patients (heavy smokers with COPD versus heavy smokers without COPD) will provide information on which factors (biomarkers, including pneumoproteins, in serum and induced sputum) are related to tobacco-induced COPD.

**Discussion:**

In total, 3133 individuals (2122 from St. Petersburg and 1012 from Arkhangelsk) aged 35–70 years agreed to participate in this study and met the inclusion criteria. In total, 2974 participants met the quality criteria for spirometry, and 2388 reversibility tests were performed. A cohort of newly defined obstructive pulmonary disease patients (247 persons) was established for follow-up investigation.

The RESPECT study will provide information regarding the prevalence of COPD in the north-west region of the Russian Federation. Moreover, the comprehensive RESPECT database will enable us to explore new research questions, provide novel insight into the risk factors and different phenotypes of COPD, and contribute to an improved understanding of the reasons why some heavy smokers develop the disease whereas others do not.

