## Background

Chronic obstructive pulmonary disease (COPD) remains a major public health problem in the 21st century. COPD is one of the leading causes of morbidity and mortality worldwide and results in an economic and social burden that is both substantial and increasing [1].

In the Russian Federation (RF), COPD represents more than 55 % of all pathologies of the respiratory system [2]. At present, approximately 2 million cases of COPD have been reported in the RF, but the actual number is estimated to be approximately 11 million [3, 4]. Several attempts to estimate the prevalence of COPD in different regions of the RF have been undertaken. These studies revealed significant differences in the prevalence of COPD based on sex, age, ecological conditions, socioeconomic status, and smoking habits, resulting in prevalence rates ranging from 1.8 to 32.0 % [5, 6]. Therefore, there is a consensus that the prevalence of COPD in the RF is underestimated and that additional reliable data are needed.

Smoking is a major risk factor for COPD, and this behavior is highly prevalent in the RF. A total of 39.1 % of all Russians (43.9 million) are current smokers (60.7 % of males and 21.7 % of females) [7]. Higher-educated Russians (vocational secondary: 41.3 %, higher education: 38.1 %) are more frequent smokers than less-educated Russians (primary: 18.0 %). Smoking is also more prevalent among urban populations (40.2 %) compared with rural populations (35.9 %).

Occupational hazards and both outdoor and indoor pollutants are also important risk factors for COPD [8–11].

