The aim of our study is to gain a better understanding of the prevalence, pathogenesis and symptoms of early COPD. This study seeks to address the following specific objectives/research questions: 1) to estimate the prevalence of AL and COPD in adults 35-70 years of age in St. Petersburg and Arkhangelsk based on sex, age, environmental conditions, socioeconomic status and smoking status; 2) to compare the prevalence of COPD in the study population based on the GOLD and LLN criteria; 3) to identify the diagnostic value of various signs, symptoms and background characteristics for the diagnosis of COPD; 4) to determine whether differences in background characteristics, inflammatory biomarkers and pneumoproteins are evident between smokers with and without COPD; and 5) to describe co-morbidity, functionality and global health status in a cohort of newly diagnosed COPD patients.

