### Setting

Two northwestern RF cities (St. Petersburg and Arkhangelsk) were selected for the RESPECT study. The population sizes of St. Petersburg and Arkhangelsk have been estimated as 4,869,600 citizens (1st January, 2011) [29] and 356,500 citizens (1^st^ January, 2010), respectively [30].

Fifteen primary care centers were invited to participate in this study. These centers are located in different areas of these cities (some in highly polluted areas, others in less polluted areas) and were selected to provide adequate coverage of the different districts.

Fifteen investigators (10 from St. Petersburg and 5 from Arkhangelsk) were recruited (predominantly doctors and two highly educated nurses). All investigators received study information, including a detailed study protocol and recent guidelines on COPD, and participated in a three-week course on spirometry and the clinical diagnosis and management of obstructive lung diseases.

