**Fig. 3 Fig3:**
[figure not shown]
Age and sex distribution of the RESPECT population

**Table 1 Tab1:** Background characteristics of the RESPECT population according to the sex

Characteristics	Total, *n* = 3133	Male, *n* = 996	Female, *n* = 2137
		(31.8 %)	(68.2 %)
Demographic			
Age, mean ± SD	54.0 ± 9.25	53.8 ± 9.52	54.2 ± 9.13
35-44	620 (19.8)	210 (21.1)	410 (19.2)
45-54	830 (26.5)	259 (26.0)	571 (26.7)
55-64	1278 (40.8)	387 (38.9)	891 (41.7)
65-70	405 (12.9)	140 (14.1)	265 (12.4)
Smoking status			
Total	3114	991	2123
Never smoker	1625 (52.2)	264 (26.6)	1361 (64.1)^a^
Current smoker	917 (29.4)	456 (46)	461 (21.7)^a^
Ex-smoker	572 (18.4)	271 (27.3)	301 (14.2)^a^
Socioeconomic status			
Total	3114	991	2123
Total score^b^, mean ± SD	10.71 ± 2.52	10.81 ± 2.58	10.68 ± 2.49
Occupational hazard	2912	934	1978
Working at dusty job > 1 year	854 (29.3)	361 (38.7)	493 (24.9)^a^
Exposed to gas or chemical fumes	782 (26.9)	349 (37.4)	433 (21.9)^a^
Indoor exposure to biomass fuels			
Gas stove use	3114	991	2123
None	1023 (32.9)	329 (33.2)	694 (32.7)
Lower use (1–6 times/week)	171 (5.5)	103 (10.4)	68 (3.2)^a^
Higher use (>7 times/week)	1920 (67.1)	559 (56.4)	1361 (64.1)^a^
Wood/coal stove use	3113	991	2123
None	2325 (74.7)	705 (71.1)	1620 (76.3)
Lower use (1–6 times/week)	535 (17.2)	204 (20.6)	331 (15.6)^a^
Higher use (>7 times/week)	253 (8.1)	82 (8.3)	171 (8.1)
Current respiratory diseases (means by patient)	3059	967	2092
COPD	43 (1.4)	21 (2.2)	22 (1.1)
Asthma	179 (5.9)	23 (2.4)	156 (7.5)^a^
Emphysema	11 (0.4)	8 (0.8)	3 (0.1)^a^
Chronic bronchitis	322 (10.5)	91 (9.4)	231 (11.0)

^a^Significant differences (*P* < .05) within the sex group (*p*-value for Pearson Chi-square test)

^b^SEC (socioeconomic status) total score compute as a sum of marital status, education, income and occupation

The RESPECT population differed from the total population of the north-west region of the RF [55] with respect to age and sex (Fig. 4). The RESPECT population includes more women than the average population in the north-west region (68.2 % versus 55.3 %, respectively, *P* < 0.05), as well as more participants aged 55–70 years (53.7 % versus 35.3 %, respectively, *P* < 0.05). The RESPECT population includes less current and ex-smokers than the average Russian population [7] (47.8 % versus 53.9 %, respectively, *P* < 0.05). The smoking status of the two populations (total and within the sex groups) is presented in Fig. 5.

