## Discussion

The RESPECT study was designed to attain a better understanding of the epidemiology of AL among the population of the north-west region of Russia based on the GOLD and LLN criteria and to examine the pathophysiological changes in the lungs in smokers without AL during the early stages of COPD.

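### The article claims prevalence for the whole north-west region, but only two cities are sampled, and its only age-sex benchmark is the regional census, not those cities

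*Protocol article*

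**What the plan says.** Two target populations appear in the Protocol article.

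- **The region.** The Abstract (Discussion) states: "The RESPECT study will provide information regarding the prevalence of COPD in the north-west region of the Russian Federation". The opening of the main Discussion presents the study as designed to describe the "epidemiology of AL among the population of the north-west region of Russia".
- **The two cities.** The first objective, at the end of the Background, is "to estimate the prevalence of AL and COPD in adults 35-70 years of age in St. Petersburg and Arkhangelsk". The Conclusion repeats that scope. The Setting says: "Two northwestern RF cities (St. Petersburg and Arkhangelsk) were selected for the RESPECT study", and adds: "Fifteen primary care centers were invited to participate in this study". It places these centers in different parts of the two cities. The Population section draws participants at random from the lists of those 15 centers.

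In the Results, after Table 1, the sample is compared with an outside population: "The RESPECT population differed from the total population of the north-west region of the RF". The caption of Fig. 4 gives the source as the census for the North-West region. The Sensitivity analysis section plans post-stratification and reweighting to test the prevalence figures, and does not name the population that supplies the margins.

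**The concern.** A prevalence estimate describes the population from which people could be drawn. Here that is adults aged 35–70 on the lists of centers in two cities. Residents of other towns and of rural areas had no chance of selection. Weighting by age and sex can correct the mix of those who were sampled, but it cannot represent people outside the frame if their prevalence differs within age-sex groups.

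The Background gives reason not to assume that it is the same. It reports that COPD prevalence in Russia varies with ecological conditions, socioeconomic status and smoking, and says: "Smoking is also more prevalent among urban populations".

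Two things are at stake. Readers of the Abstract may take a two-city figure as a regional one. And if the regional census were carried over as the weighting margin, the result would be neither the Objective 1 estimate nor a regional estimate with adequate coverage.

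**Working it through.** **1. The plan's own figure.** The prevalence sample size uses n = Z²P(1−P)/d² with Z = 1.96, P = 0.08 and d = 0.01: 3.8416 × 0.0736 / 0.0001 = 2827.4, rounded up to 2828. It reproduces. The formula concerns sampling error only and says nothing about who is covered, so the point does not rest on it.

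**2. The sections side by side.**

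| Element | Section | Population |
|---|---|---|
| Prevalence claim | Abstract, Discussion | North-west region |
| Stated design purpose | Discussion, opening | North-west region |
| Objective 1 | Background, end | Two cities, ages 35–70 |
| Setting | Setting | Two cities |
| Sampling frame | Population | Lists of 15 centers in those cities |
| Restated objective | Conclusion | Two cities, ages 35–70 |
| Age-sex benchmark | Results after Table 1, Fig. 4 | Census of the whole region |
| Weighting margin | Sensitivity analysis | Not named |

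The objective, setting, frame and conclusion agree. The two regional statements and the benchmark do not match them. No section samples elsewhere in the region or argues for carrying the city results over to it.

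**3. Does the choice of reference population matter?** The gaps against the region are large: 68.2 % women against 55.3 %, and 53.7 % aged 55–70 against 35.3 %. To illustrate what a margin can do, take ever-smoking from Table 1:

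- Men: (456 + 271)/991 = 0.7336
- Women: (461 + 301)/2123 = 0.3589
- As sampled: 1489/3114 = 47.8 %
- Standardised to the regional sex mix (44.7 % men, 55.3 % women): 0.447 × 0.7336 + 0.553 × 0.3589 = 52.6 %

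The shift is 4.8 points for smoking from the sex margin alone. This shows that the choice of reference is not a formality. It does not show how far a two-city margin would differ from the regional one, because the article gives no age-sex distribution for the cities.

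**4. Can the city-versus-region gap be sized?** It would be the share of the region living outside the two cities multiplied by the difference in prevalence. The Setting gives the city populations (4,869,600 and 356,500), but the article gives neither the region's total nor any COPD prevalence for the rest of it. Both factors are missing, so no figure follows.

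**The case against.** The strongest reply is that the operative plan is already consistent. The objective, setting, frame and conclusion name the two cities, and no regional estimator or sample size is set out. The Abstract's wording is soft, and the Results report openly that the sample differs from the region. This stands in part: no calculation is wrong. It does not remove the point, because the main Discussion gives the region as the design target, and disclosing age and sex differences does not address people who could not be sampled.

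Several stronger readings are tempting and are not supported:

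- **That the plan weights to the regional census.** A reader might infer this because it is the only age-sex reference given. The Sensitivity analysis section commits to no margin, and the Results use the census descriptively. Smoking is compared there with a national survey instead.
- **That a bias can be quoted.** Assuming 30–60 % of the region lives outside the cities, with prevalence 2–3 points different, gives 0.30 × 2 = 0.6 to 0.60 × 3 = 1.8 points. None of these inputs is in the article. The one urban-rural figure is current smoking, 40.2 % against 35.9 %, a gap of 4.3 points. For smoking alone to produce a 2–3 point COPD gap, prevalence in smokers would have to exceed that in non-smokers by about 47–70 points (2/0.043 to 3/0.043).
- **That the Abstract's Methods add a third target.** They refer to two regions, but the bracket names the same two places as Objective 1.
- **That sampling from primary-care lists is itself the flaw.** The Population section says the lists are territorial, so they may approximate residents.
- **That each city must be reported before any pooled figure.** This is a reporting preference and does not follow from this point.

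**Conclusion.** The point holds as a mismatch between the claimed population and the sampled one. The design supports prevalence for adults aged 35–70 in St. Petersburg and Arkhangelsk. It does not support prevalence for the north-west region, and the regional census is the wrong benchmark for the stated objective. Its use as a weighting margin remains a risk until the margin is named. The size of any difference between cities and region is unknown, and its direction is not established either.

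The conclusion assumes that the 15 centers' lists do not reach materially beyond the two cities. The article gives no catchment boundaries, but nothing in it suggests that they do. The matter goes beyond wording, because it narrows what the study can conclude and changes the reference population. It does not undermine the two-city objective.

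**What to change.** 1. In the Abstract (Discussion) and the opening of the main Discussion, limit the prevalence claims to adults aged 35–70 in St. Petersburg and Arkhangelsk, in line with Objective 1 and the Conclusion.
2. In the Results after Table 1 and in Fig. 4, compare the sample with the two cities' own age-sex distribution at ages 35–70.
3. In the Sensitivity analysis section, name that same distribution as the post-stratification margin.

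The cost is a different census table and a narrower conclusion. No new data collection and no change to the sample size are needed.

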**Clinical trial registration:**

NCT02307799 (the release date: 12/01/2014)

## Background

Chronic obstructive pulmonary disease (COPD) remains a major public health problem in the 21st century. COPD is one of the leading causes of morbidity and mortality worldwide and results in an economic and social burden that is both substantial and increasing [1].

In the Russian Federation (RF), COPD represents more than 55 % of all pathologies of the respiratory system [2]. At present, approximately 2 million cases of COPD have been reported in the RF, but the actual number is estimated to be approximately 11 million [3, 4]. Several attempts to estimate the prevalence of COPD in different regions of the RF have been undertaken. These studies revealed significant differences in the prevalence of COPD based on sex, age, ecological conditions, socioeconomic status, and smoking habits, resulting in prevalence rates ranging from 1.8 to 32.0 % [5, 6]. Therefore, there is a consensus that the prevalence of COPD in the RF is underestimated and that additional reliable data are needed.

Smoking is a major risk factor for COPD, and this behavior is highly prevalent in the RF. A total of 39.1 % of all Russians (43.9 million) are current smokers (60.7 % of males and 21.7 % of females) [7]. Higher-educated Russians (vocational secondary: 41.3 %, higher education: 38.1 %) are more frequent smokers than less-educated Russians (primary: 18.0 %). Smoking is also more prevalent among urban populations (40.2 %) compared with rural populations (35.9 %).

Occupational hazards and both outdoor and indoor pollutants are also important risk factors for COPD [8–11].

Price et al. developed a symptom-based questionnaire for the identification of patients at increased risk of airflow limitation (AL) [12, 13]. Their COPD diagnostic questionnaire consists of 8 items and discriminates between subjects with and without AL. These authors concluded that their questionnaire could be used to identify patients displaying a high likelihood of exhibiting AL and that combining this questionnaire with spirometry could potentially improve the efficiency and accuracy of COPD diagnoses in primary care. However, Kotz et al challenged these findings and demonstrated that this questionnaire is likely not useful as a diagnostic tool for the identification of patients with an increased risk of AL in a high-risk population consisting of middle-aged current smokers with a smoking history of ≥ 10 pack-years [14]. A recent systematic review of the diagnostic value of patient history and physical examination concluded that the available evidence is very limited and does not accurately determine which characteristics of patient history and physical examination are appropriate to be used by physicians to identify patients suspected to exhibit COPD who require spirometry [15].

A recently proposed combined COPD assessment tool [1] not only focuses on the degree of AL but also considers symptoms, the degree of dyspnea (measured using the Modified Medical Research Council Dyspnea Scale (mMRC)) [16, 17] and the number of COPD exacerbations. However, it remains commonly accepted that AL, as measured by spirometry, is a hallmark of COPD [1] and is essential for the early detection of the disease [18].

Initially, AL was defined as a ratio of the forced expiratory volume in 1 s (FEV_1_) to the forced vital capacity (FVC) that was below the fifth percentile of a large healthy reference group (the statistically defined lower limit of normal (LLN)) [19]. Subsequently, the European Respiratory Society/American Thoracic Society (ERS/ATS) COPD guidelines and the Global Strategy for Diagnosis, Management and Prevention of COPD (GOLD) proposed the use of a fixed ratio of 0.7 (FEV_1_/FVC < 0.7) [20]. Lung function tests using 80 % predicted and fixed threshold values to determine whether a result is abnormal misdiagnosed 20 % of patients referred for pulmonary function assessment [19]. This misclassification is avoided by using the LLN, which is based on the fifth percentile value [20]. The LLN may be less than an FEV_1_/FVC of 0.7 after approximately 45 years of age. In 2005, an ATS/ERS pulmonary function interpretation guideline strongly recommended the use of the LLN for FEV_1_/FVC to define AL [20]. Recently, the GOLD committee acknowledged that “using LLN values for FEV_1_/FVC that are based on the normal distribution and classify the bottom 5 % of the healthy population as abnormal is one way to minimise the potential misclassification” [1, 20].

The Global Lung Function Initiative (GLI, ERS Task Force) published multi-ethnic reference values for spirometry in the 3- to 95-year age range in the 2012 global lung function equations [21]. Currently, the spirometry prediction equations for the 3- to 95-year age range (including the appropriate age-dependent LLN) are available and can be applied globally to different ethnic groups [22].

At present, it remains unclear why some smokers develop COPD whereas others do not. Furthermore, it is unclear why COPD occasionally develops in non-smokers. Certain inflammatory and immune parameters differ between smoker and non-smoker COPD patients and correlate with AL, especially with the decline in the FEV_1_ [23]. COPD is characterized by increased levels of inflammatory cytokines, such as interleukins (ILs) IL-1β, IL-4, IL-8, and IL-12 and other proteins, such as chemotactic cytokine (C-C motif ligand, CCL) CCL5, CCL3, macrophage migratory inhibitor factor (MIF), soluble intercellular adhesion molecule (sICAM), granulocyte chemotactic activity (GCA) and surfactant protein D (SP-D), in exhaled breath condensate. Simultaneous significant decreases in IL-1β, IL-6, IL-8, IL-12, tumor necrosis factor (TNF-α) and Clara cell protein have been detected in stable COPD patients compared to active smokers who did not exhibit clinical signs of COPD [23]. The type of inflammatory process in COPD is not well characterized and may vary among patients. COPD displays elements of bronchitis, airway hyperreactivity, pulmonary emphysema and inflammation in variable proportions, and it appears unlikely that all patients with COPD exhibit the same underlying disease processes [24].

The determinants of persistent systemic inflammation among patients with COPD include age, body mass index (BMI), smoking and AL [25]. In addition to smoking, certain pathogenic mechanisms, such as chronic inflammation, abdominal obesity, and physical inactivity, are most likely involved in the development of COPD [26].

Presently, major advances in the understanding of the mechanisms underlying COPD have been made, but many important questions about the pathogenesis and diagnosis of COPD remain. Further research is needed to resolve these questions [27], presenting new challenges for researchers.

Recently, a series of recommendations for epidemiological studies of COPD were published in a task force report by the ERS [28]. The authors recommended using clear diagnostic criteria and standardized methods to examine COPD and all potential risk factors for COPD. Studies of COPD in the population at large should also assess various phenotypes of this disease.

This report suggests measuring as many different characteristics of COPD patients as possible to contribute to an understanding of the disease that is well beyond spirometry classifications.

The aim of our study is to gain a better understanding of the prevalence, pathogenesis and symptoms of early COPD. This study seeks to address the following specific objectives/research questions: 1) to estimate the prevalence of AL and COPD in adults 35-70 years of age in St. Petersburg and Arkhangelsk based on sex, age, environmental conditions, socioeconomic status and smoking status; 2) to compare the prevalence of COPD in the study population based on the GOLD and LLN criteria; 3) to identify the diagnostic value of various signs, symptoms and background characteristics for the diagnosis of COPD; 4) to determine whether differences in background characteristics, inflammatory biomarkers and pneumoproteins are evident between smokers with and without COPD; and 5) to describe co-morbidity, functionality and global health status in a cohort of newly diagnosed COPD patients.

